### Allocation/randomization

#### Sequence generation and allocation concealment mechanism

The allocation sequence will be computer-generated by VieDoc using permuted blocks with varying block sizes. Patients will be randomized immediately after baseline assessment to RA or SA (see Fig. 1). Patients allocated to the RA will further be randomized to the intervention and control group, while patients randomized to the SA will self-select allocation to either intervention or control group.

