### Objectives

The main objective of this study is to determine the effectiveness of a self-management program aiming to support recovery trajectories and prevent chronic problems in patients with moderate to severe traumatic injuries. A self-management support program, SEMPO, was developed for patients in the sub-acute phase of moderate to severe traumatic injury.

The SEMPO is a group-based intervention that includes eight weekly sessions focusing on a specific topic, and it is theoretically based on self-management principles and established rehabilitation strategies. The intervention comprises several ingredients, including psychoeducation, guided skills mastery, learning and practicing helpful compensatory strategies and problem-solving techniques, as well as sharing coping experiences.

We hypothesize that compared to the control group, SEMPO will result in:Increased self-efficacy in managing health problemsImproved health, reduced disability, and use of fewer health care resourcesImprovement in target problem areas and lower burden of trauma-related problemsEvidence on the relative effectiveness and cost-effectiveness of SEMPO compared to standard services

We further anticipate that:Self-selected partaking in the intervention will enhance self-efficacy and level of function of the self-nominated outcome, as well as maximize adherence and reduce potential attrition biasImplementation fidelity will be high and the intervention will be deemed acceptable by participants and therapists

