### Trial design

The proposed study is a pragmatic parallel-group randomized controlled trial (RCT) with a mixed method design. The study design includes the classical RCT design with randomization to intervention and control arm. In addition, patients could be randomized to a self-selection arm where they can choose to be allocated to either the intervention or control arm. This is considered as an exploratory part of the study to explore whether the patients’ treatment preferences will maximize adherence, reduce potential attrition bias, and influence the intervention results [20]. Hence, this innovative pragmatic RCT seeks to align the study design to patient-centered treatment, where the influence of patient treatment preferences on intervention effect and adherence will be explored.

Patients who consent to participate will undergo a baseline assessment (T1) before being randomized to either the randomization (RA) arm or self-selection (SA) arm. Follow-up assessments will take place after the completion of the 8-week SEMPO program (T2) and at 3 (T3) and 6 months (T4) after completion of the intervention, with similar follow-up time points for the control group. A feasibility study will be conducted before the full-scale RCT. Additionally, a process evaluation will be performed. This mixed-method design is in line with an updated recommendation by the British Medical Research Council [21].

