### Statistical methods

Sociodemographic, clinical, and injury-related characteristics and outcome data will be presented using descriptive statistics. Independent sample *t*-test will be used for between-group mean comparisons for normally distributed continuous data, and Mann–Whitney *U*-tests for skewed data. For comparison of categorical data, chi-square tests or Fisher’s exact test will be used. To investigate the effectiveness of the intervention on self-efficacy, symptom burden and disability, and patient impression of change, mixed-effect models will be used to account for repeated measurements by patients. Time and time-by-treatment interaction will be used as fixed effects in these models. The linear mixed effects model will give estimated mean values for all time points (T1, T2, T3, and T4), changes from baseline, and between-group differences from baseline with 95% confidence intervals. The models will first be performed separately within the classical RCT and self-selected groups, and if reasonable, merged together. Possible confounders or mediators will be included when analyzing the self-selected group. To reduce the risk of dropout bias, the analyses will be based on an “intention to treat” principle by analyzing all patients in the group they were randomized to, regardless of whether they participated in or completed the intervention. A significance level of 5% will be used.

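### Patients are randomised to RA or SA, but no stated analysis compares the two arms; the only SA analysis is a SEMPO-control contrast confounded by choice

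*Protocol article*

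**What the plan says.** Under Sequence generation and allocation concealment mechanism, "Patients will be randomized immediately after baseline assessment to RA or SA". RA patients are then randomised again to SEMPO or control, whereas "patients randomized to the SA will self-select allocation to either intervention or control group".

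Trial design explains why SA exists: to explore whether "treatment preferences will maximize adherence, reduce potential attrition bias, and influence the intervention results". Objectives turns this into an expectation: "Self-selected partaking in the intervention will enhance self-efficacy and level of function of the self-nominated outcome", together with better adherence and less attrition bias.

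Statistical methods sets the analysis: "The models will first be performed separately within the classical RCT and self-selected groups, and if reasonable, merged together". On model terms it says "Time and time-by-treatment interaction will be used as fixed effects in these models", and on self-selection "Possible confounders or mediators will be included when analyzing the self-selected group". Process evaluation analysis records participation and non-compliance without comparing RA with SA. Managing non-adherence and missing data compares complete cases with dropouts, again not by arm. SA is called exploratory in Trial design, Sample size and Discussion.

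**The concern.** The first randomisation is what allows SA to answer a question about choice. It makes the two arms comparable at entry, so a difference between them in retention or outcome can be attributed to being offered the choice. The analysis as stated does not use it. It asks the same question in each arm, SEMPO against control, and in SA that compares people who wanted the programme with people who did not.

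That within-SA contrast mixes the treatment effect with differences between choosers and decliners and with any effect of getting one's choice. Adjustment for unnamed confounders cannot be relied on to separate these, and adjusting for mediators would remove part of the effect being estimated. The intention-to-treat rule does not help, because SA patients are randomised to no treatment. For retention and adherence, no arm comparison is stated at all.

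Half the sample is at stake: 220 − 110 = 110 patients recruited to a question that the stated models do not answer. A merged estimate would also carry the self-selection bias into the effectiveness result.

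**Working it through.** **Inputs from the article.** Total 220 (Abstract). From Sample size: RA 110, difference 0.6, SD 1, 80% power, 5% level, 20% attrition. SA is therefore 220 − 110 = 110, and evaluable patients per arm are 110 × 0.8 = 88. I assume two-sided tests, since sidedness is not stated.

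**The plan's own figure.** The normal approximation gives n = 2 × (1.960 + 0.842)² × 1² / 0.6² = 43.6, so 44 per group. The t-test version gives 44.6, so 45 per group and 90 in total. The stated 45 and 90 reproduce. They size SEMPO against control within RA, not RA against SA.

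**What RA versus SA could detect.** Detectable difference = (1.960 + 0.842) × √(2/n), in SD units.
- n = 88 per arm: 2.802 × 0.1508 = 0.42 SD.
- n = 110 per arm (no losses): 2.802 × 0.1348 = 0.38 SD.

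**Retention, 110 v 110.** Retention is known for everyone randomised. With the arcsine approximation, h = 2·arcsin√p₁ − 2·arcsin√p₂ and power = Φ(h√(110/2) − 1.960). RA attrition is the plan's 20%; the SA rates are assumptions.

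| SA attrition | h | Power |
|---|---|---|
| 15% | 0.132 | 16% |
| 10% | 0.284 | 56% |
| 7% | 0.392 | 83% |

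**Power of the within-SA contrast.** With 88 evaluable and share s choosing SEMPO (assumed), SE = √(1/(88s) + 1/(88(1−s))) and power for 0.6 = Φ(0.6/SE − 1.960).

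| s | SE | Power |
|---|---|---|
| 50% | 0.213 | 80% |
| 70% | 0.233 | 73% |
| 80% | 0.267 | 61% |
| 90% | 0.355 | 39% |

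The aim of equal power in SA, stated under Sample size, therefore depends on a near-even choice.

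**Bias of the within-SA contrast.** If choosers and decliners differ in prognosis by d (assumed 0.3 SD, range 0.1 to 0.5), the within-SA estimate shifts by d. With an even choice, RA and SA have equal weight (each 1/(1/44 + 1/44) = 22), so a merged estimate shifts by d/2: 0.15, range 0.05 to 0.25, against the target of 0.6.

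**What the RA-versus-SA outcome contrast contains.** RA gives SEMPO to half its patients and SA to share s. A treatment effect of 0.6 alone moves the SA mean by 0.6 × (s − 0.5): 0.06 at 60%, 0.12 at 70%, 0.18 at 80% and 0.24 at 90%, with no preference effect at all. Comparing the SA mean with RA means weighted by s and 1 − s removes that shift. Treating s as fixed, SE = √(1/88 + s²/44 + (1−s)²/44), and the detectable difference is 0.42 at s = 50%, 0.44 at 70% and 0.46 at 80%. Removing the share effect costs little precision.

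**The case against.** The strongest reply is that SA is openly exploratory, that this is a condensed article, and that an unseen SAP may hold the arm comparisons. The authors also show awareness of confounding: they plan covariates for SA, make merging conditional, and contrast SA with the more rigorous RA. This limits the weight of the point and confines it to what the article states. It does not remove it, because the article names the questions and fixes a model structure that cannot answer them.

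Four stronger readings are tempting and should not be taken.
- A reader might infer that adherence and attrition are left to a confounded comparison. The article states no comparison for either; the confounding lies in the SA outcome model and any merge.
- A reader might infer that the preference hypothesis will be judged by setting the SA effect beside the RA effect. The article says only that the models are "performed separately within the classical RCT and self-selected groups" first, not that their difference is the test.
- A reader might take RA versus SA as the preference effect itself. It estimates the effect of offering choice, including any change in the share receiving SEMPO.
- A reader might expect adherence to be compared as randomised. Session attendance exists only for SEMPO recipients, and those in SA are self-selected.

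It is also fair that precision is limited. A detectable 0.42 SD is 70% of the difference planned for the whole intervention, and nothing in the article suggests that choice alone does so much.

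**Conclusion.** The point holds in a limited form. The stated analysis has no RA/SA term and no arm comparison of retention or attendance, and its only SA contrast is confounded by choice. The first-stage randomisation therefore goes unused in the article.

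The bias could be material: 0.3 within SA and 0.15 in an evenly weighted merge, under an assumed 0.3 SD prognostic gap. The alternative is unbiased for the effect of offering choice but only moderately precise: about 0.42 SD for T4 self-efficacy, and useful power for retention only if attrition falls from 20% to around 7%. The SA attrition rates, the choice shares and the prognostic gap are all assumptions, since the article gives none.

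The primary RA comparison and its sample size are untouched unless a merged estimate is presented as the main result. The change is worth making because it costs almost nothing and lets SA address its stated purpose.

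**What to change.** In Statistical methods, name the following as the exploratory analysis of SA:

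1. RA versus SA as randomised, all patients, for T4 retention and T4 self-efficacy. State that the outcome contrast estimates the effect of offering choice, including any change in the share receiving SEMPO.
2. Two-stage preference and selection estimators from the four cell means and the SA choice share, with bootstrap intervals, to separate that share from preference.
3. Session attendance among SEMPO recipients by arm, descriptive only, because SA recipients are self-selected.

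Label within-SA and merged SEMPO-control estimates as observational, and state that the RA-only estimate remains the primary result.

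The cost is wording and some analysis time. Retention, outcome and participation data are already planned. Trial status puts the end of recruitment at an estimated end of 2026, so the wording can be fixed before results are seen. The downside is the modest precision shown above, so these results should stay exploratory and be reported with intervals.

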**Fig. 1 Fig1:**
[figure not shown]
Participant timeline

#### Blinding/masking

Blinding of interventionists or patients will not be possible, but outcome assessors will be blinded for study allocation at follow-ups (T2–T4). The data analyst will be unaware of group allocation during the statistical analyses by assigning dummy codes to the study arms.

## Methods: data collection, management, and analysis

### Data collection methods

All patients will complete a baseline assessment before randomization procedures. The baseline assessments will be administered by the two PhD candidates ([name] and [name]). The patients can either answer the outcome questionnaires electronically or by pen and paper All outcome assessors will be trained in the administration of the data collection methods. A description of study outcome measures is displayed in Table 1. To ensure retention and complete follow-ups, the outcome assessors will be flexible with regards to scheduling the follow-up appointments. If patients wish to discontinue after the baseline assessment (T1), we will ask permission to use the baseline data in sensitivity analysis.

### Data management

Information about patients will be managed by healthcare professionals/project assistants adhering to Norwegian law on confidentiality [53]. All data material will be recorded with a participant ID, where only the local project group members will have access to the code list linking ID and patients. All data will be stored in VieDoc on a secured server at OUH, and individuals will not be identifiable in publications. The data will be stored securely in the VieDoc software and deleted 5 years after completion of the project.

The telehealth solution for self-chosen digitally delivered intervention will be provided by the Norwegian Health Net [54], a videoconference platform delivered by Pexip, Oslo, Norway. The platform is encrypted, and pin codes are used to access virtual meeting rooms, which are locked after start of meeting. Therapists will run the telehealth sessions using their work computers and a screen with an integrated speaker and camera optimized for videoconference. The videoconference solution is risk-assessed and approved for clinical use by the OUH.

### Statistical methods

Sociodemographic, clinical, and injury-related characteristics and outcome data will be presented using descriptive statistics. Independent sample *t*-test will be used for between-group mean comparisons for normally distributed continuous data, and Mann–Whitney *U*-tests for skewed data. For comparison of categorical data, chi-square tests or Fisher’s exact test will be used. To investigate the effectiveness of the intervention on self-efficacy, symptom burden and disability, and patient impression of change, mixed-effect models will be used to account for repeated measurements by patients. Time and time-by-treatment interaction will be used as fixed effects in these models. The linear mixed effects model will give estimated mean values for all time points (T1, T2, T3, and T4), changes from baseline, and between-group differences from baseline with 95% confidence intervals. The models will first be performed separately within the classical RCT and self-selected groups, and if reasonable, merged together. Possible confounders or mediators will be included when analyzing the self-selected group. To reduce the risk of dropout bias, the analyses will be based on an “intention to treat” principle by analyzing all patients in the group they were randomized to, regardless of whether they participated in or completed the intervention. A significance level of 5% will be used.

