**Other outcome measurements for all patients**			
Resilience	Resilience Scale for Adults [39]	Level of Resilience	T1–T4
Health status (HRQL)	EuroQol five-dimensional questionnaire (EQ-5D) [40]	Health-related quality of life	T1–T4
Individual injury-related problem areas	Target Outcomes [27]	Individual target problem areas and their severity	T1–T4
Evaluation of changes and intervention satisfaction	Patient Global Impression of Change [41] Intervention satisfaction (intervention group only)	Level of satisfaction with intervention/ change	T2–T4 T2
Disability	WHO Disability Assessment Scale (WHODAS) [42]	Health and disability	T1–T4
General functioning	Glasgow Outcome Scale – Extended (GOSE) [43]	Global outcome	T1–T4
Communication	Communication with physicians [15] Health Literacy Questionnaire [44]	Communication with health care providers Capacity to obtain and understand health information	T1–T4
Health care utilization	Type and frequency of health care services received using a patient-reported survey. Health care services comprise secondary care services, primary care, specialist care, rehabilitation, and home- and community-based care, assistive devices, and informal care	Number of visits and type of health care services	T1–T4

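### Without a treatment term, the mixed model as usually read assumes a common first-visit mean, which has no basis in the self-selected or merged analyses and does not fit impression of change, which has no T1

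*Protocol article*

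**What the plan says.** All of the model text is in the Statistical methods section of the protocol article.

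- Outcomes covered: "self-efficacy, symptom burden and disability, and patient impression of change, mixed-effect models will be used".
- Fixed effects: "Time and time-by-treatment interaction will be used as fixed effects in these models".
- Output promised: "The linear mixed effects model will give estimated mean values for all time points (T1, T2, T3, and T4), changes from baseline", together with between-group differences from baseline.
- Data sets: "The models will first be performed separately within the classical RCT and self-selected groups, and if reasonable, merged together".
- Extra provision for SA: "Possible confounders or mediators will be included when analyzing the self-selected group".

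Three facts from elsewhere in the article bear on this. Data collection methods states: "All patients will complete a baseline assessment before randomization procedures". The section on sequence generation and allocation concealment states: "patients randomized to the SA will self-select allocation to either intervention or control group". Table 2 schedules Patient Global Impression of Change (PGIC) at T2–T4, with no T1 assessment.

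The article does not say whether time is categorical or continuous, how the interaction is coded, or whether T1 means are meant to be equal.

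**The concern.** Listing time and time-by-treatment while leaving out treatment is the usual way to write a baseline-constrained longitudinal model. Its justification is randomisation after T1: the groups are then draws from one population at T1, so a common mean is correct and gains precision. The article carries the same specification to two settings where that argument is missing.

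1. **SA and the merged set.** Patients choose their group, so nothing makes the T1 means equal. A constrained model would report one T1 mean for two groups that may differ, and would measure each group's change from that shared value.
2. **PGIC.** The first available visit is T2, after the programme. If T2 takes the place of the reference visit, the end-of-programme effect is fixed at zero. This applies in RA as well as SA, because T2 follows treatment.

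At stake are the SA and pooled estimates and the PGIC results. The primary outcome in RA is not at stake.

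**Working it through.** **Planning figures, used only for scale.** The Sample size section gives a difference of 0.6, SD 1, 80% power and a 5% level (two-sided assumed). The normal formula gives 2 × (1.96 + 0.84)² × 1² / 0.6² ≈ 43.6, so 44 per group. The t-test version gives 44.6, so 45, which matches the article.

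**Step 1: does the wording impose equal T1 means?** Four visits by two groups make 8 cell means.
- Categorical time with the full interaction has 8 columns and rank 8, the same space as a model with a treatment term. Nothing is constrained.
- The same model with the first-visit interaction term dropped has 7 columns. The groups share the T1 mean.
- Continuous time from 0 has 3 columns. The groups share the intercept.

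The answer depends on coding, which the article does not give.

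**Step 2: size in SA under the constrained reading.** Assumptions not in the documents: SD 1, a constant correlation ρ between visits, complete data, ρ of 0.3 to 0.7, and a T1 gap of 0.2 to 0.5 SD. Write d1 and d4 for the true group differences at T1 and T4. The constrained model estimates d4 − ρ·d1. If the gap persists unchanged, d4 = d1 and the difference in change is zero, but the model returns (1−ρ) × gap:

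| Gap | ρ = 0.3 | ρ = 0.5 | ρ = 0.7 |
|---|---|---|---|
| 0.2 | 0.14 | 0.10 | 0.06 |
| 0.3 | 0.21 | 0.15 | 0.09 |
| 0.5 | 0.35 | 0.25 | 0.15 |

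A simulation with 45 per group and 4,000 runs gave these rates of declaring a T4 effect at the 5% level:

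| Gap | ρ = 0.3 | ρ = 0.5 | ρ = 0.7 |
|---|---|---|---|
| 0 | 5.0% | 5.0% | 4.7% |
| 0.2 | 10% | 8% | 6% |
| 0.3 | 18% | 13% | 9% |
| 0.5 | 41% | 29% | 16% |

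The zero-gap row is the RA case and shows no inflation.

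**Step 3: is freeing T1 free of bias in SA?** No. With T1 free, the change contrast is d4 − d1. If choice depends on the T1 score and the gap regresses to the mean with no treatment effect, then d4 = ρ·d1. The constrained contrast is then ρ·d1 − ρ·d1 = 0, which is right, and the change contrast is −(1−ρ)·d1. With d1 = −0.5 and ρ = 0.5 that is a false +0.25.

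**Step 4: PGIC.** The Statistical methods section promises T1 means and changes from baseline for outcomes that include impression of change, while Table 2 has no T1 assessment of it. These conflict under any coding. If T2 were used as the reference visit, a constant effect δ at T2–T4 would be reported as 0 at T2 and δ − ρδ = (1−ρ)δ at T3 and T4. For an illustrative δ of 0.6 SD the T4 estimate is 0.42, 0.30 or 0.18 at ρ = 0.3, 0.5 or 0.7.

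**The case against.** The strongest reply is that the sentence imposes nothing. With categorical time and a full interaction, every visit has its own treatment difference, and coding is a detail that a condensed article may leave to the analysis plan. That stands as far as it goes. A reader might infer that the model necessarily forces equal first-visit means, or that it sets the PGIC effect at T2 to zero; the text supports neither as a certainty. But the article does fix the list of fixed effects. That list is the customary form of the constrained model, and two analysts following it could obtain materially different SA results. The PGIC conflict does not depend on coding.

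Second, the article recognises that SA groups may not be comparable: it plans confounder adjustment there and makes pooling conditional. This also stands. The adjustment may reduce a T1 gap, but it does not lift the constraint unless it removes the gap, and the covariates are not named.

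Third, the constrained contrast is in effect a baseline-adjusted one, and step 3 shows a case where it is right and the change contrast wrong. A reader might infer that freeing T1 is the correct SA analysis; under self-selection that cannot be claimed.

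Fourth, SA is exploratory and PGIC is among the other outcomes. That limits the weight of the point.

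**Conclusion.** The point holds in a limited form. The PGIC conflict is in the text itself: T1 means and changes from baseline are promised for an outcome with no T1. The common-T1-mean problem holds under the usual reading of the specification and not under a full categorical interaction. Under the usual reading, SA and merged models would misreport T1 means and changes from baseline by group. A persisting gap would shift the SA T4 contrast by 0.06 to 0.35 SD, against a planning effect of 0.6 with SD 1. The gaps and correlations behind that range are assumptions, as are constant correlation and complete data, and the shift is an error only if the gap persists rather than regresses. A reader might infer that the primary comparison is compromised. It is not: T1 precedes randomisation, and the constraint is valid for self-efficacy in RA. The change should be made, but the primary result does not depend on it.

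**What to change.** - State that the common T1 mean applies only to RA outcomes measured at T1, and give the coding of time and the interaction.
- In SA and merged models, include a treatment term so that T1 means are free, and keep the planned confounder adjustment. Report the baseline-adjusted contrast beside the contrast in change, and say that neither is unbiased in general when patients choose their group.
- For PGIC, drop the T1 mean and change from baseline, and estimate a treatment effect at each of T2, T3 and T4. An ordinal model is optional.

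The cost is a few sentences and slightly lower precision in the exploratory SA analysis. The primary RA analysis is unchanged.

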### Sample size

The sample size was estimated based on the primary outcome, the Trauma Coping Self-Efficacy Scale questionnaire [26]. The questionnaire is a 9-item scale answered on a scale ranging from 0 (not capable) to 7 (totally capable). A mean difference in the Trauma Coping Self-Efficacy Scale of 0.6 between baseline and follow-up between the groups is considered as a clinical relevant difference (ref). In order to detect a mean between-group difference of 0.6 with an estimated standard deviation of 1, equal allocation to both groups, 80% power, and a significance level of 5%, we will need to include a minimum of 45 patients in each group and a total of 90 participants [51]. With an assumed attrition rate of 20%, 110 patients will be included (i.e., 55 patients in each group). The sample size calculation was done based on the classical randomization arm (RA), and we aim to achieve the same power in the self-selection (SA) arm. However, the SA is considered an exploratory part of this study to evaluate the influence of patients’ treatment preferences. According to a previous longitudinal study at OUH, approximately 310 patients with trauma-related disability from 18 to 72 years of age may meet the inclusion criteria [52]. Based on previous studies, approximately 70–80% will be eligible for inclusion, resulting in 218–249 eligible patients per year.

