## Discussion

This self-management intervention study targets patients with moderate to severe physical trauma in the sub-acute phase and patients at risk of long-term symptom burden and injury-related disabilities. The innovative and newly designed self-management program; SEMPO is a complex intervention and entails ingredients aiming to enhance patients’ self-efficiency in managing difficulties they experience in daily life in the sub-acute phase following injury. The program includes therapeutic ingredients such as psychoeducation, action planning, training in problem-solving, and peer-sharing experience in managing injury-related consequences. The program focuses on establishing and reviewing personal action plans, facilitating individual skills enhancement, and sharing experiences to enhance social encouragement. To our knowledge, this is the first study to investigate the effect of a self-management program tailored to patients with moderate to severe physical trauma in the sub-acute phase of recovery. It is also the first study to bring the self-management concept into a structured and manualized group-based intervention in the trauma population. The intensity of the program, with eight weekly sessions, allows thorough training in goal setting and adaptive management of difficulties. The intervention is in line with person-centered treatment.

The inclusion of a self-selection arm in a pragmatic RCT is an innovative way to incorporate the influence patients’ preferences have on the effectiveness of the intervention. This approach brings the experimental design for clinical interventions closer to real-world scenarios and aligns with the notion of shared decision-making. The self-selection arm is an explorative part of the study, while the classic randomization arm (patients allocated by randomization to either intervention or control group), will follow a more traditional rigorous experimental design.

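### The effectiveness models may be merged across randomised and self-selected patients without fixing the randomised-only estimate as primary

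*Protocol article*

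**What the plan says.** The Statistical methods section gives the models their purpose: "To investigate the effectiveness of the intervention on self-efficacy, symptom burden and disability, and patient impression of change, mixed-effect models will be used". Self-efficacy is the primary outcome, with T4 as its endpoint (Outcome measures). The same section then sets the order of analysis: "The models will first be performed separately within the classical RCT and self-selected groups, and if reasonable, merged together". No criterion for merging is given, and one 5% significance level is stated for everything.

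Three other statements bear on this:

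- **How SA patients are allocated** (Sequence generation and allocation concealment mechanism): "patients randomized to the SA will self-select allocation to either intervention or control group".
- **Status of the SA:** the Sample size section says "the SA is considered an exploratory part of this study to evaluate the influence of patients’ treatment preferences", and the Discussion says "The self-selection arm is an explorative part of the study". The Abstract and Trial design say the same in substance.
- **Basis of the sample size:** "The sample size calculation was done based on the classical randomization arm (RA"), with the same power hoped for in the SA.

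Two safeguards appear in Statistical methods. One is covariate adjustment: "Possible confounders or mediators will be included when analyzing the self-selected group". The other is the intention-to-treat rule of "analyzing all patients in the group they were randomized to, regardless of whether they participated in or completed the intervention".

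**The concern.** In the RA, the SEMPO–control difference estimates the effect of being offered SEMPO. In the SA, the same difference is that effect plus whatever distinguishes people who choose SEMPO from people who decline it, plus any effect of getting one's preference. The Objectives section itself anticipates that choosing the intervention will improve self-efficacy, and studying preference is the reason the SA exists. A merged model puts that expected influence into the effectiveness estimate.

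Neither safeguard covers the merged model. Adjustment is mentioned only for the self-selected analysis, the covariates are unnamed, and adjusting for mediators can itself distort a treatment effect. The intention-to-treat rule refers to the group a patient was randomised to, but SA patients were never randomised to SEMPO or control. The stated fixed effects are time and time-by-treatment, with no term for arm.

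At stake is which number answers the main question. About half of the merged sample would have chosen its treatment. The merged estimate would look more precise than the randomised one, and nothing in the statistical section ranks the two.

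**Working it through.** **1. Reproduce the plan's own figure.** Inputs from Sample size: difference 0.6, SD 1, 80% power, 5% level (two-sided assumed; one-sided would give 35 per group).
- Normal formula: n = 2 × (1.960 + 0.842)² / 0.6² = 43.6, so 44 per group. The t-test version gives 44.6, so 45. The stated 45 per group is reproduced.
- With 110 RA patients and 20% attrition, 110 × 0.8 = 88 completers, or 44 per group. Power is then 80.4% (normal) or 79.5% (t-test). The RA alone carries the primary question at about the planned power.

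**2. Bias and type I error of a merged estimate.** The total of 220 implies about 110 SA patients, so 88 completers there too. The documents give neither the choice split nor the size of any selection effect, so both are assumed: splits of 50:50 and 75:25, and a residual difference b between SEMPO choosers and control choosers of 0 to 0.4 points at T4 after adjustment. There is no treatment effect.
- RA variance: vR = 1/44 + 1/44 = 0.0455.
- SA variance: vS = 0.0455 at 50:50 (44 v 44); vS = 1/66 + 1/22 = 0.0606 at 75:25.
- SA weight: w = (1/vS) / (1/vS + 1/vR) = 0.50 or 0.429.
- Merged SE = 1/√(1/vS + 1/vR) = 0.151 or 0.161.
- Bias = w × b. Type I error = P(|Z + w·b/SE| > 1.96).

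| b | 50:50 bias | 50:50 error | 75:25 bias | 75:25 error |
|---|---|---|---|---|
| 0 | 0 | 5.0% | 0 | 5.0% |
| 0.2 | 0.10 | 10.2% | 0.09 | 8.3% |
| 0.3 | 0.15 | 16.9% | 0.13 | 12.5% |
| 0.4 | 0.20 | 26.4% | 0.17 | 18.6% |

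A negative b gives the same two-sided error, with bias in the opposite direction. Against the 0.6 target, a bias of 0.20 is one third.

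This calculation compares treatments within each arm before combining, as a model with an arm term would. The stated model has no such term. A simulation without one (40,000 runs per setting) gave 9.9%, 16.6% and 25.5% at b = 0.2, 0.3 and 0.4 with an even split. At 70:30, with the whole difference placed on the SEMPO choosers, it gave 32.4% at b = 0.4. The 26% is therefore not a ceiling under every assumption.

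**3. Would checking that RA and SA agree make merging safe?** Suppose merging is allowed when the arm-by-treatment interaction is not significant at 5% (assumed; the plan gives no rule). The SE of the difference between the two effects is √(vR + vS) = 0.302 at 50:50 and 0.326 at 75:25.
- True difference 0.6: z = 1.99 or 1.84, power 51% or 45%.
- True difference 0.3: z = 0.995 or 0.92, power 17% or 15%.

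In the simulation at b = 0.3, this check still merged in about 83–84% of trials (50:50 and 70:30 splits). Type I error for the resulting estimate was 16.1% at 50:50.

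**4. Choosing between results.** With b = 0 and an even split, always merging keeps error at 4.9%. Merging only after a non-significant interaction gives 6.3%. If either the RA or the merged result could be claimed, it is about 8%. The RA test alone stays at about 5% in every setting.

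**The case against.** The strongest reply is that the randomised comparison is always produced. The models are fitted separately first, so merging is an optional later step. The SA is called exploratory in four places (Abstract, Trial design, Sample size, Discussion) and the trial is sized on the RA, so a reader may fairly take the RA as the main analysis. This stands. A reader might infer that the plan abandons randomisation, or that the merged figure is meant as the headline result; the documents say neither.

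Second, inflation of type I error is conditional. With no residual selection effect and merging always done, the error is about 5%. Larger figures need an assumed chooser difference and split. The direction is unknown too, since patients with greater difficulties might be the ones who choose SEMPO. The models also estimate differences in change from baseline, which removes part of any stable difference between choosers. All of this stands, so inflation cannot be stated as a fact about the plan.

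Third, it is tempting to say that a clinically relevant disagreement between RA and SA would usually be missed. At the plan's own 0.6 it would be missed about half the time.

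Fourth, a merging criterion and covariate list may sit in an analysis plan not shown, and the analyst is to work with dummy codes (Blinding/masking). The absent criterion alone would therefore be weak ground. But dummy codes hide labels, not how far the two arms agree. And the protocol goes beyond silence: it provides for moving self-selected patients into an effectiveness model without ranking the result.

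**Conclusion.** The point holds in a limited form. The statistical section permits a merged effectiveness estimate, on the primary outcome and at the same 5% level, in which about half the patients chose their treatment. It names no primary estimate, which sits badly with the exploratory status of the SA and the RA-based sample size. The RA-only estimate is sound; what is exposed is the merged estimate and any results-driven choice between the two.

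Under the arm-stratified assumptions in steps 2 and 3 of the working, bias runs from 0 to about 0.2 points in either direction and type I error from about 5% to 26%. These figures illustrate the risk and do not predict it, because the documents give neither the selection effect nor the split. That agreement between the arms is a poor licence to merge rests on less: only the plan's SD, the implied numbers and the assumed split.

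**What to change.** Add one sentence to Statistical methods: the between-group contrast at T4 in the classical randomisation arm is the sole confirmatory estimate of effectiveness, whatever the self-selected or merged results show. Then do one of two things:

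- delete the merging clause; or
- keep a merged model labelled exploratory and non-randomised, with terms for arm (RA/SA) and arm-by-treatment, adjusted for named baseline confounders and not for mediators, and with no effectiveness claim based on it.

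The change needs no extra patients: the 110 planned for the RA give about 80% power at 88 completers. The cost is the loss of a pooled estimate that looks more precise. It should be made before outcome results are seen; Trial status estimates that recruitment will run to the end of 2026.
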